**Upgrading the reference hospital paediatric services**

It has been proposed that the WHO guidelines for severe malnutrition are feasible in rural African hospitals, but at the condition of implementing other interventions that build human capital and strengthen the health system .

In order to adequately manage cases of severe malnutrition at the district hospital as recommended by the WHO, the following actions will be undertaken:

- Case detection in the primary health facilities,

- Reference in the district hospital,

- Inpatient care and management of complications in the district hospital,

- Contre-reference in the primary health care as soon as the complication are treated,

- Regular supportive supervision of the primary health care by the district hospital team

- Clinical audit of all case admitted in the district hospital.

Cases of severe malnutrition and cases of moderate malnutrition with complications will enter in program with two phases (the inpatient program and the outpatient program).. Severe malnutrition is defined as W/H<70% or presence of bilateral oedema. Complications are defined as one of the following conditions: anorexia, acute respiratory infection, severe dehydration, severe anaemia, apathy.

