**Ensuring ambulatory care for moderately malnourished children**

All case of moderate acute malnutrition (70 %< W/H <80%) will enter in an ambulatory program emphasizing an appropriate child-centered counselling on feeding practice and care. Home visits will be made once a week to assess feeding practices and child specifics problems, and needs. Although following the main recommendations reported in table 3, the rehabilitation will be thus tailored to each case. Two important aspects will be stressed: frequency and energy density of meals. Means to improve these two aspects will be defined in accounting for the purchase power and the food accessibility of each family. Families will be encouraged to use local foods, e.g. add 5 ml of oil in the gruel ration and provide the child with snacks several times during the day. RTUF could be purchased at the health centre. The follow-up of the nutritional status will be made once a week in the health centre. During every visit the anthropometric measures will be taken (weight height, MUAC) to follow the evolution and the presence of other diseases will be assessed for providing adequate treatment.

A child will be confirmed cured when his/her W/H>80% and growth curve ascending for two consecutive weighing (2 consecutive weeks).

A particular attention will be paid to children not responding to the programme in order to adapt rapidly and adequately the management. Children who have not gained weight after two weeks of follow-up will be thoroughly examined to assess the presence of chronic pathologies (cardiac malformation, renal deficiency, HIV infection, pulmonary tuberculosis) and begin an adequate treatment, if possible. If a chronic pathology is ruled out, the family will be encouraged to use RTUF. Children who developed a medical complication and/or loose weight will be transferred to the hospital.

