**Admission criteria:**

**Children from 6 to 59 months for which the P/T<70% or MUAC <110 mm**

**Check for complications and do the appetites test**

**Children with complication and/or failing appetite test.**

1. Bilateral pitting oedema grade 3*(severe oedema)

OR

2. MUAC<110 mm AND bilateral pitting oedema grades 1 or 2 (marasmic kwashiorkor)

OR

3. MUAC<125 mm OR bilateral pitting oedema grades 1 or 2

AND one of the following:

Anorexia

Lower respiratory tract infection

Severe palmer pallor

High fever

Severe dehydration

Fails appetite

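### Section 3.3.4 gives two conflicting lists of the complications that bring a malnourished child into hospital care, and the transfer rules do not say which one applies

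*Protocol*

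**What the plan says.** All of this is in Protocol section 3.3.4 (Improving the Structural dimension).

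- **Text on upgrading the reference hospital.** The programme entry rule is: "Cases of severe malnutrition and cases of moderate malnutrition with complications will enter in program with two phases". Shortly after comes a definition, worded as complete: "Complications are defined as one of the following conditions: anorexia, acute respiratory infection, severe dehydration, severe anaemia, apathy".
- **Decision schema under Admission criteria.** One box is labelled "Children with complication and/or failing appetite test". Its criteria 1 and 2 rest on oedema grade and MUAC alone. Criterion 3 starts from "MUAC<125 mm OR bilateral pitting oedema grades 1 or 2" and adds any one of six signs: anorexia, "Lower respiratory tract infection", "Severe palmer pallor", high fever, severe dehydration and "Fails appetite".
- **Schema box for children with appetite and no complication.** It sets a MUAC or oedema condition and also requires appetite and that the child be clinically well. That last term is not defined.
- **Phase 2 outpatient treatment.** Severe cases that have no medical complication and have passed the appetite test may go straight to outpatient care. A child who later develops a complication needing inpatient treatment goes back to Phase 1.
- **Ambulatory care for moderate cases.** "Children who developed a medical complication and/or loose weight will be transferred to the hospital".
- **Schema box for outpatient therapeutic care.** A failed appetite test or a new medical complication again leads back to inpatient care.

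**The concern.** One term, complication, decides whether a malnourished child is managed in hospital or near home. It has two non-identical lists a few pages apart, and nothing ranks one above the other. A health worker who follows the text and one who follows the schema can place the same child differently.

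What is at stake is the safety and consistency of a rule that primary-care staff must apply. The protocol itself asks in its background how such programmes can run with less qualified staff. In section 3.3.3 it reports that the IMCI package is not being implemented despite earlier training. It also plans two-monthly audits of malnourished children's files and a clinical audit of all hospital admissions. An auditor with two definitions cannot say whether a given referral followed the protocol.

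**Working it through.** The protocol gives no figure to reproduce here and no statistical calculation applies. The check sets the two lists side by side and traces children through the rules.

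**Step 1. Align the lists.**

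| Sign | Hospital text | Schema, criterion 3 | Result |
|---|---|---|---|
| Anorexia | yes | yes | match |
| Severe dehydration | yes | yes | match |
| Severe anaemia / severe pallor | anaemia | pallor | near equivalent |
| Respiratory infection | any acute | lower tract only | different scope |
| Apathy | yes | no | text only |
| High fever | no | yes | schema only |
| Failed appetite test | no | yes | schema list only, partly covered elsewhere |

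Text: 3 matching + 1 different in scope + 1 text only = 5 signs. Schema: 3 matching + 1 different in scope + 2 schema only = 6 signs.

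The appetite item is a smaller difference than the count suggests. For severe cases going directly to Phase 2, the outpatient rules already require the test to be passed. For moderate cases the item stays open, because the text list has anorexia but not the test.

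**Step 2. Which children are affected.** Children meeting criterion 1 or 2 are placed without any listed sign, so the conflict does not touch them. The hospital text attaches its definition to moderate cases, because it enters all severe cases in the two-phase programme. Criterion 3 reaches up to a MUAC of 125 mm, the same value as the 12.5 cm at which section 3.3.3 has community workers refer children in order to detect moderate cases. The two lists therefore meet most directly on moderate cases. The Phase 2 rule extends the question to severe cases by asking whether a complication is present.

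**Step 3. Trace single signs.** Each child below has one sign only and passes the appetite test. The moderate child has W/H between 70% and 80%, MUAC between 110 and 125 mm and no oedema. The severe child has W/H below 70%, MUAC below 110 mm and no oedema.

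| Child and sign | Using the text's definition | Using the schema |
|---|---|---|
| Moderate, high fever | no complication: ambulatory care | criterion 3 met: inpatient box |
| Moderate, apathy | complication: two-phase programme | criterion 3 not met; outpatient box not met on MUAC or oedema: no box |
| Moderate, respiratory infection above the lower tract | complication: two-phase programme | as for apathy: no box |
| Severe, high fever | no complication: may go directly to Phase 2 | criterion 3 met: inpatient box |
| Severe, apathy or respiratory infection above the lower tract | complication: not directly to Phase 2 | criterion 3 not met; outpatient only if judged clinically well, otherwise no box |

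High fever gives opposite placements. Apathy and the wider respiratory item give a clear rule in the text and an unclear or missing one in the schema.

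**Step 4. Look for a tie-breaker.** The Phase 2 return rule, the transfer rule for moderate cases and the schema's outpatient box all use a complication as the trigger. None lists the signs again or points to either list.

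**The case against.** The strongest reply is that this is a mismatch of wording with less effect than it seems.

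- **The schema does not plainly send apathetic or coughing children to outpatient care.** A reader might infer that it does. The documents do not support that, because the outpatient box also requires the child to be clinically well. This part of the reply stands: for apathy and for the wider respiratory item the result is ambiguity, not a clear opposite placement. But the condition is undefined, and a child who fails it can be left in neither box, so it does not restore the text's rule.
- **Acute respiratory infection may be shorthand for the lower-tract item.** It sits among otherwise serious signs, so this is possible. The protocol does not say so, and high fever and apathy would remain unreconciled.
- **Training, supervision and audit would settle it.** Sections 3.3.1 to 3.3.3 and the hospital text provide all three. They lower the risk, but they need one list to teach and audit against.
- **Frequency.** A reader might take the baseline figure of 39% of children sick in the previous two weeks to mean that these signs will often decide placement. It covers any illness in all children aged 0-59 months and says nothing about these signs in malnourished children.
- **Comparability of results.** A reader might infer that case-management results cannot be compared across centres. Nothing shows that centres will follow different pages. Effectiveness of acute malnutrition case management is an output in the programme theory (section 3.6), not one of the primary or secondary outcomes listed there.

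**Conclusion.** The contradiction is real and lies in current text. Of the signs compared, three agree (one as a near equivalent), three conflict (apathy, high fever, scope of respiratory infection), and one, the appetite test, conflicts in the lists but is partly closed by the Phase 2 rule. High fever is the clearest case.

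The conclusion rests on two readings. First, the schema box for complications or a failed appetite test leads to inpatient care. The figure's arrows are not visible in the text at hand, but the box labels support this. Second, criterion 3 covers moderate cases. The schema's opening line admits only severe cases, so this could be disputed; that is a separate inconsistency in the anthropometric thresholds. Even if criterion 3 applied to severe cases only, the conflict would remain through the Phase 2 rule.

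How many children would be affected cannot be stated, because the protocol gives no frequency for any of these signs. Sample size and the primary analysis are untouched. The point concerns safety and consistent delivery. It should be corrected, but it does not threaten the trial's main comparison.

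**What to change.** The responsible clinicians should reconcile the hospital text and criterion 3 of the schema into one list of complications. It should appear once and be referred to in the Phase 2 outpatient rules, the transfer rule for moderate cases and both schema boxes that govern outpatient care. The same edit should say what clinically well means in relation to that list, so that every child falls in one box, and whether the appetite test counts as a complication or as a separate condition. The intervention centres should be trained on the single list, and the audits should use it. Which signs belong on it is a clinical decision on which this review takes no view.

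The cost is protocol wording and the training aid. No extra data, staff or participants are needed.

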**The inpatient program in the district hospital paediatric services**

The treatment will be essentially based on the OMS standard protocols . However, the WHO guidelines recommend a W/H>90% as criterion of a successful treatment. To reach such a target takes several weeks, exposing the children to possible cross-infections in the hospital and increasing the burden of the parents. Within the current intervention, children will be referred to the primary health centre level for an ambulatory follow-up as soon as the complications are treated and the WH>70%, i.e. when the child is not anymore severely malnourished although not yet completely cured (see point 3.3).

a) Inpatient-treatment phase 1 using only F75 Formula

- Admitted children should be registered and all information recorded in a [Multichart](javascript:plainWindow1()) including the target weight for discharge (WHO/NCHS table).

-Admitted children should be provided with a systematic medical examination and given routine medicine.

- Only F75 will be use during this phase

- Daily surveillance of weight will measured and plotted on the multichart.

- The degree of oedema will assessed and noted in the Multichart,

- Body temperature will measured twice a day

- Standard clinical signs (stool, vomiting, dehydratation, cough, respiration and liver size) will assessed

- Breastfeeding children should always get the breast milk before the diet and on demand.
- Preparation of F75 to give during this phase will based on the class of weight

-The WHO Feeding Table will be used

b) Inpatient-treatment transition using only RUTF

- Daily surveillance of the child remains exactly the same in Transition phase as it was in Phase 1. The expected rate of weight gain is about 6g/kg/day if all the food is taken by the children and there is not excessive malabsorption.

- Breastfeeding children should always get the breast milk before the diet and on demand.
 - Routine antibiotics should be continued after transferred from Phase 1 for another four days.

**Move the children back to phase 1:**

- If the child gains weight more rapidly than 10g/kg/day
- If there is increasing oedema
- If child suddenly develops oedema
- If liver size increases rapidly
- If child develops signs of fluid overload
- If child develop signs of abdominal distension
- If child gets significant re-feeding diarrhoea so there is weight loss
- If naso-gastric tube is needed
- If complication arise that necessitates an intravenous infusion

***Progress the child to phase 2***

- If the child has a good appetite. Taking 90% of the prescribed RUTF
- If the child has lost the oedema entirely

**Phase 2 outpatient treatments in the primary health center**

All children with severe acute malnutrition without medical complications and that have passed the [appetite test](http://motherchildnutrition.org/malnutrition-management/info/appetite-test.html) can go directly to Phase 2.

Children that are admitted directly to Phase 2 as out-patients should be provided with a systematic medical examination and given routine medicine.

Children transferred from [in-patient treatment](http://motherchildnutrition.org/malnutrition-management/management-severe-acute-malnutrition/in-patient-treatment-phase-2.html) should be registered as "transferred from".

Surveillance of the children:

- Every week, weight will measure, entered and plotted on the Child Card.
- Every week, the presence of bilateral [oedema](http://motherchildnutrition.org/early-malnutrition-detection/detection-referral-children-with-acute-malnutrition/screening-for-acute-malnutrition.html" \l "Bilateral pitting oedema) will assess and noted in the Child Card.
- Every week, body temperature is measured and noted in the Child Card.
- Every week, standard clinical signs (stool, vomiting, dehydration, cough, respiration and liver size) will assessed and noted in the Child Card.
- Every week, [Mid-Upper Arm Circumference (MUAC)](http://motherchildnutrition.org/early-malnutrition-detection/detection-referral-children-with-acute-malnutrition/screening-for-acute-malnutrition.html" \l "Mid-upper Arm Circumference (MUAC)) will take.
- Every month measurement of height/length

**RUTF** is provided as take-home therapeutic food for malnourished children only.

- The amount of RUTF provided to the caregiver will base on the class of weight and on the necessary quantity required to last until the next visit to the out-patient site.
- Use the RUTF Feeding Table
- Breastfeeding children will always give Breast-Milk before RUTF.
- Move the child in phase 1 (in-patient)
- If the child develops any medical complications that demand in-patient treatment
- If the child has severely reduced appetite
- If the child increases/develops oedema
- If the child develops “refeeding diarrhoea” sufficient to lead to weight loss,
- If the child does not respond to the treatment
- If there is a weight loss for 2 consecutive weighing sessions
- If there is a weight loss of more than 5% of body weight at any visit,
- If the weight stays for three consecutive weighing sessions.

**Ensuring ambulatory care for moderately malnourished children**

All case of moderate acute malnutrition (70 %< W/H <80%) will enter in an ambulatory program emphasizing an appropriate child-centered counselling on feeding practice and care. Home visits will be made once a week to assess feeding practices and child specifics problems, and needs. Although following the main recommendations reported in table 3, the rehabilitation will be thus tailored to each case. Two important aspects will be stressed: frequency and energy density of meals. Means to improve these two aspects will be defined in accounting for the purchase power and the food accessibility of each family. Families will be encouraged to use local foods, e.g. add 5 ml of oil in the gruel ration and provide the child with snacks several times during the day. RTUF could be purchased at the health centre. The follow-up of the nutritional status will be made once a week in the health centre. During every visit the anthropometric measures will be taken (weight height, MUAC) to follow the evolution and the presence of other diseases will be assessed for providing adequate treatment.

A child will be confirmed cured when his/her W/H>80% and growth curve ascending for two consecutive weighing (2 consecutive weeks).

A particular attention will be paid to children not responding to the programme in order to adapt rapidly and adequately the management. Children who have not gained weight after two weeks of follow-up will be thoroughly examined to assess the presence of chronic pathologies (cardiac malformation, renal deficiency, HIV infection, pulmonary tuberculosis) and begin an adequate treatment, if possible. If a chronic pathology is ruled out, the family will be encouraged to use RTUF. Children who developed a medical complication and/or loose weight will be transferred to the hospital.

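### The protocol gives two outpatient tracks, with different RUTF supply and different responses to static weight, for a child stepped down from inpatient care at W/H 70-80%

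*Protocol*

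**What the plan says.** All of this is in protocol section 3.3.4 (Improving the Structural dimension).

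- **Opening paragraph.** Severe cases are to be treated at the reference level until they are moderate, and moderate cases are to be managed at the health centre.
- **Upgrading the reference hospital paediatric services.** "Severe malnutrition is defined as W/H<70% or presence of bilateral oedema". On entry: "Cases of severe malnutrition and cases of moderate malnutrition with complications will enter in program with two phases", the phases being inpatient and outpatient.
- **The inpatient program.** "children will be referred to the primary health centre level for an ambulatory follow-up as soon as the complications are treated and the WH>70"%, described as the point "when the child is not anymore severely malnourished although not yet completely cured".
- **Phase 2 outpatient treatments.** Children coming from inpatient treatment are registered as transfers. RUTF "is provided as take-home therapeutic food for malnourished children only", in a quantity set by weight class and sufficient until the next visit. Weight that is static over three consecutive weighings returns the child to Phase 1.
- **Ensuring ambulatory care for moderately malnourished children.** Every case with W/H above 70% and below 80% enters a programme built on counselling and local foods, and "RTUF could be purchased at the health centre". After two weeks without gain the child is examined for chronic disease; if none is found, the family is encouraged to use RUTF. The cure rule is here: "A child will be confirmed cured when his/her W/H>80% and growth curve ascending for two consecutive weighing".

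**The concern.** On reaching the health centre, a child who leaves the hospital with W/H in the 70-80% band fits both the Phase 2 description and the moderate-malnutrition description. Under one, therapeutic food is handed over in a set amount. Under the other, the family may buy it. The steps that follow a failure to gain weight differ as well.

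Staff in the intervention centres are to be trained on prescribing RUTF (section 3.4), so they need a single rule. Without one, two centres could follow the protocol faithfully and still supply and follow the same child differently. That is first a patient-safety concern. It also blurs two things the protocol wants to learn: whether acute malnutrition is managed effectively (an output in the programme theory, Figure 3) and whether severe malnutrition care becomes cheaper (a target in section 2).

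**Working it through.** No formula applies. The check is whether one child satisfies both sets of rules, and whether the text ranks them.

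| | Phase 2 outpatient treatment | Ambulatory care, moderate malnutrition |
|---|---|---|
| Who | Transfers from inpatient care; uncomplicated severe cases passing the appetite test | Every case with 70% < W/H < 80%, no exception stated |
| RUTF | Provided to take home, by weight class, until next visit | Can be bought; no quantity given |
| No weight gain | Static for three consecutive weighings: back to Phase 1 | Two weeks without gain: work-up, then encouragement to use RUTF |
| Home visits | None stated in the subsection | Weekly |
| Height | Monthly | Every weekly visit |
| Cure rule | None stated in the subsection | W/H>80% with a rising curve at two weighings |

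**Step 1: the bands.** Step-down requires W/H>70%. The moderate programme takes 70% < W/H < 80%. The intersection is 70% < W/H < 80%, which is the entire moderate band (80 − 70 = 10 percentage points). Every child stepped down in that band is also a transfer from inpatient care, so both columns apply. A child stepped down at W/H of 80% or more is outside the overlap.

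**Step 2: complicated moderate cases.** These enter the two-phase programme by the hospital subsection's own rule. If moderate means W/H 70-80%, as the moderate subsection defines it, they are in the overlap from admission, without any change in W/H.

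**Step 3: Phase 2 outpatients.** A child admitted directly to Phase 2 with W/H below 70% enters the moderate band on passing 70%. The Phase 2 subsection says when to return a child to Phase 1. It does not say whether a child crossing 70% stays on the track.

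**Step 4: timing of the two responses.** Phase 2 weighing is weekly. Three consecutive weighings span 2 intervals × 1 week = 2 weeks if the first weighing is counted, or 3 weeks if the three follow a baseline. The other track acts at two weeks. So at about the same moment, one subsection sends the child back to inpatient care and the other keeps the child in ambulatory care for a work-up.

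**Step 5: does anything rank them?** The opening paragraph of 3.3.4 and the inpatient subsection treat the stepped-down child as no longer severe and refer to ambulatory follow-up, which is the moderate subsection's term. The two-phase rule and the registration of transfers point to Phase 2. The inpatient subsection's cross-reference is to point 3.3, which in the table of contents is the whole intervention section. No sentence gives one track precedence.

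**The case against.** The best reply is that the two subsections serve two populations. Severe and complicated moderate cases follow the two-phase programme, whose second phase is the Phase 2 outpatient subsection. The inpatient material has its own list for progressing a child to Phase 2, and the flowchart labels Phase 2 as RUTF follow-up in primary facilities. The moderate subsection has a separate heading, says who enters it, and never says that a Phase 2 child leaves on crossing 70%. The different measurement schedules fit this reading.

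It is plausible and may be what was meant, but it is nowhere stated. The moderate subsection takes every case in its band without exception, and two other places reclassify the stepped-down child as no longer severe. The ambiguity stands.

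Other parts of the reply succeed and limit the point:

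- A reader might infer two conflicting RUTF doses. The moderate subsection gives no quantity, so the contrast is between a ration that is provided and food the family may buy. The Phase 2 text says provided, not free.
- A reader might infer that a child admitted on MUAC below 110 mm with W/H already above 80% counts as cured under the W/H rule. That rule sits in a subsection whose entry band such a child never meets, so it is not shown to apply.
- A reader might infer that Phase 2 has no exit rule at all. The flowchart has lost its arrows in the text at hand and contains a discharge box, and the plan leans on feeding tables and WHO protocols not reproduced here. Absence cannot be asserted firmly.
- Both tracks have weekly follow-up and send a child to hospital for complications and for weight loss (with different triggers), which tempers the safety concern without removing it.
- Some local adaptation by each centre's nutrition team is planned (section 3.4), so not all variation between centres would be a departure from the plan.

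**Conclusion.** The contradiction is real and specific. For a child stepped down at W/H between 70% and 80%, including a complicated moderate case, the protocol supports two tracks that differ in RUTF supply and in the response to static weight, and it ranks neither. The same uncertainty meets a Phase 2 outpatient whose W/H passes 70%.

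The overlap covers the full 70-80% band. How many children fall in it cannot be worked out from the protocol. The conclusion rests on reading the moderate subsection's entry rule as written, without an unstated exception for children already in the two-phase programme.

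The consequences are a patient-safety concern and greater difficulty in interpreting case-management effectiveness and cost. A reader might go further and call those results uninterpretable, or expect the primary comparison to be distorted. The document supports neither. Case-management effectiveness is a programme-theory output and is not listed among the primary or secondary outcomes in section 3.6. The sample-size outcome is wasting in a random population sample aged 0-24 months, and no effect on it is shown.

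**What to change.** Reconcile the opening of 3.3.4, the hospital and inpatient subsections, Phase 2, and the moderate-malnutrition subsection, so that the protocol and the training material:

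1. name one track for children stepped down from inpatient care, including moderate cases admitted with complications;
2. name one track for Phase 2 outpatients whose W/H passes 70%;
3. say whether the W/H>80% cure rule applies to Phase 2 children, including those admitted on MUAC or oedema under the flowchart's admission criteria.

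The clinical team decides the content; no supply, return or discharge rule is proposed here. The cost is a wording change and an updated training sheet. The downside is that RUTF supply may need re-estimating once the track is settled.
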